**2.6 What are the proposed methods for protecting against other sources of bias?**

To reduce the possibility of selection bias, all children of the appropriate age with the primary diagnosis of acute gastroenteritis will be approached to participate. There will be some selection bias in that the most ill children may die in the first few hours after admission (before enrollment), and these children might have a higher probability of having a treatable enteric infection; however, many of these children would probably be judged as potentially having ‘bacterial sepsis’ and therefore would not be eligible for enrollment anyway. Allocation concealment will be centralized using the web-based system. Loss to follow-up will be minimized by ensuring that all potential participants live locally, have a means of getting in contact, and are aware of follow-up procedures. Observer/interviewer bias at the time of outcome measurement will be minimized by precise standardization of measurement protocols; in any case, all of the important outcomes (mortality and growth) are objective measures, and therefore less susceptible to observer bias.

**2.7 What is the proposed frequency and duration of follow-up?**

The research assistant will contact the participant 7-14 days after discharge from hospital to ensure that the caregivers remember the timing of the second follow-up visit and to answer any relevant questions about the study. The research assistant will then contact the participant again 60 days after enrollment to assess the primary outcome and weigh and measure the participant, if applicable. It would be optimal to have another follow-up visit approximately 12 months after enrollment; this may not be feasible with the funds we have acquired for this project, but we will ask participants for consent to approach them should moneys become available.

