**2.2 What is the population under study?**

**2.2.1 Inclusion criteria.**

Children aged 3 to 60 months admitted to the Princess Marina Hospital paediatric medical ward primarily because of acute diarrhoeal disease will be eligible. Acute diarrhoeal disease will be defined as at least three watery stools in the 24 hours preceding admission to hospital. Children with HIV infection will not be excluded. Children with severe acute malnutrition will be eligible to be included in the rapid vs delayed testing and targeted treatment arms, but will not be randomized to probiotic (or placebo).

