**2.8 What are the proposed *clinical* outcome measures?**

**2.8.1 Primary clinical outcome.** The primary outcome is mortality. If the participant dies prior to the 60-day followup, the research assistant will determine the date of death as accurately as possible.

**2.8.2 Other clinical outcomes.** Secondary outcomes will include the following: weight z-score at 60-day followup adjusted for initial weight; height z-score at 60-day followup adjusted for initial height; presence of stunting at 60-day followup; length of stay in hospital; number of days with at least three watery stools; number of days of fever in hospital; 7-day mortality; recurrence of acute diarrhoea during the 60-day followup period; re-presentation to a medical professional because of acute diarrhoea during the 60-day followup period; readmission to a paediatric medical ward during the 60-day followup period; HIV viral load (detectable/undetectable) at the next assessment within 6 months of enrollment, for those participants that are HIV positive; and environmental enteropathy score([21](#_ENREF_21)) (composite of faecal alpha-1 antitrypsin, neopterin, and myeloperoxidase) at 60 days.

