**2.9 How will the *clinical* outcome measures be measured at follow up?**

**2.9.1 Mortality.** Mortality will be ascertained by the research assistant, whether in hospital or after discharge.

**2.9.2 Secondary clinical outcomes**. Data related to secondary clinical outcomes associated with the participant’s stay in hospital (number of days of 3+ watery stools, number of days of fever, length of stay) will be abstracted from the patient chart (both physician and nursing notes) at discharge. The remaining secondary clinical outcomes will be assessed at the 60-day followup visit; the research assistant will use a calibrated scale and stadiometer to obtain precise anthropomorphic measures.

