**2.10 What are the *feasibility* outcomes, or criteria for success of this pilot study?**

The specific feasibility criteria of this pilot are:

1) to enroll at least 100 participants during the 12-month study period;

2) to ensure that >95% of participants have a rectal swab taken within 18 hours of admission;

3) to verify that >95% of rectal swabs in the experimental group are resulted within 48 hours of admission;

4) to ensure >95% of participants found to have a treatable enteric pathogen are prescribed appropriate antimicrobials;

5) to ensure that >95% of participants prescribed antimicrobials start them within 24 hours of the test being resulted;

6) to contact >95% of participants 7-14 days after discharge from hospital; and

7) to contact >90% of participants 60 days after admission to hospital.

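### Diarrhoea recurrence and re-presentation are assessed only at day 60, while the planned contact 7-14 days after discharge has no stated outcome collection, so the end of the index episode is not captured in children discharged with symptoms

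*Protocol*

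**What the plan says.** Section 2.7 sets two contacts. The first, 7-14 days after discharge, is there to "ensure that the caregivers remember the timing of the second follow-up visit and to answer any relevant questions about the study". At the second, the research assistant will "contact the participant again 60 days after enrollment to assess the primary outcome and weigh and measure the participant, if applicable".

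Section 2.8.2 lists among the secondary outcomes "recurrence of acute diarrhoea during the 60-day followup period" and "re-presentation to a medical professional because of acute diarrhoea during the 60-day followup period", and also readmission to a paediatric medical ward over the same period.

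Section 2.9.2 says how these are obtained. The in-hospital items ("number of days of 3+ watery stools, number of days of fever, length of stay) will be abstracted from the patient chart") are collected at discharge. For everything else: "The remaining secondary clinical outcomes will be assessed at the 60-day followup visit".

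The only definition of diarrhoea is the entry definition in section 2.2.1: "Acute diarrhoeal disease will be defined as at least three watery stools in the 24 hours preceding admission to hospital". Section 2.10 makes the early contact a feasibility criterion, "to contact >95% of participants 7-14 days after discharge from hospital", against more than 90% at 60 days. Section 2.13 plans chi-square tests for recurrence and for re-presentation or readmission.

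**The concern.** For episodes managed at home, a single question at day 60 means caregiver recall over most of two months. A contact that falls much closer to the index illness is already planned, but no outcome is assigned to it.

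The second part matters more. Watery-stool days are counted only up to discharge, so a child discharged with diarrhoea has no recorded end of the index episode. A later analysis plan could define a diarrhoea-free interval, but for that child it would have no resolution date to apply it to.

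Two things are at stake:

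- **Interpretation.** The probiotic benefit cited in section 1.1 is a shorter illness (a mean of 24.5 hours). If the arms differ in how many children go home unresolved, a duration effect can be read as a recurrence effect.
- **What the pilot delivers.** Section 1.2 says the pilot will assess methods of outcome assessment and event rates, and section 1.3 wants all outcomes to be reliably measurable. The bias argument in section 2.6 rests on mortality and growth being objective; caregiver-reported recurrence is outside it.

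**Working it through.** The protocol states no rate, effect or power for these outcomes, and the sample of 100 in section 2.11 is justified by feasibility alone. There is no figure to reproduce, so the check is a comparison of sections followed by two illustrations.

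**1. Sections side by side.** Section 2.8.2 limits fever days to hospital but does not limit watery-stool days; section 2.9.2 nevertheless takes both from the chart at discharge. Recurrence and re-presentation are not chart items, so they fall under the remaining outcomes at day 60. No diary, interim outcome call or record search is described for them. The monthly health-records check in section 3.2 counts admissions of children of the appropriate age with gastroenteritis; it is not an outcome source. So no planned step after discharge dates the end of the index episode.

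**2. Recall window.** Assume a stay of L = 2 to 10 days (not in the protocol), and treat admission and enrolment as the same day.

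- Early contact falls on day L + 7 to L + 14, that is day 9 to day 24.
- Recall at day 60 as planned: 60 − L = 58 to 50 days.
- Recall at day 60 if the early contact also collects outcomes: from 60 − (2 + 7) = 51 down to 60 − (10 + 14) = 36 days.
- Share of post-discharge time moved to the early contact: from 7/58 = 12% to 14/50 = 28%.

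The early contact covers the stretch in which unresolved index illness would lie, but leaves long recall for most of the follow-up.

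**3. Effect of misclassification.** Let p be true recurrence, s the share of recurrent children recalled as such, and u the share of non-recurrent children counted because of continuing index illness. The observed rate is p·s + (1 − p)·u.

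Assume p = 30% v 15% and 50 children per side of a factorial margin (half of 100; slightly fewer for the probiotic margin, because children with severe acute malnutrition are not randomised to probiotic or placebo). Use a two-sided 5% test of two proportions in the normal approximation, with mean rate p̄ and difference d:

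n = [1.96·√(2p̄(1 − p̄)) + 0.8416·√(p₁(1 − p₁) + p₂(1 − p₂))]² / d²

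For 30% v 15%: (1.1575 + 0.4889)² / 0.0225 = 120.5, so 121 per group.

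| s | u | Observed rates | Risk ratio | Power, 50 per side | n per group, 80% power |
|---|---|---|---|---|---|
| 1 | 0 | 30% v 15% | 0.50 | 43% | 121 |
| 0.8 | 0 | 24% v 12% | 0.50 | 34% | 160 |
| 1 | 0.1 | 37% v 23.5% | 0.64 | 31% | 181 |
| 0.8 | 0.1 | 31% v 20.5% | 0.66 | 22% | 272 |

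Equal under-recall lowers the rate, the absolute difference and the power but leaves the risk ratio alone. Equal counting of index illness also pulls the risk ratio towards 1.

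If u differs between arms while p is equal and s = 1, the observed difference is (1 − p)(u₁ − u₂). This is a spurious recurrence effect, proportional to a gap about which the protocol says nothing.

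**The case against.** Several points on the other side are sound.

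- A reader might infer that episodes are in fact missed and that continuing illness is counted as recurrence. The protocol does not say so. Recurrence ordinarily implies prior resolution, and the chart may show whether diarrhoea had stopped by discharge. The ambiguity is confined to children discharged with symptoms, and their number is not given.
- A reader might infer that the early contact collects nothing. Section 2.7 states a purpose and does not forbid data collection, and under section 2.9.1 a death after discharge could come to light there. No stated outcome collection is as far as the text goes.
- A reader might take the early contact as the only chance to learn when the index illness ended. The caregiver could also be asked at day 60, with poorer recall.
- The absence of a diarrhoea-free interval is not by itself a fault; it could sit in an analysis plan or case report form.
- The outcomes are any-event binaries, so a child is misclassified by forgetting only if every episode is forgotten. Visits to a professional are probably remembered better than mild episodes at home.
- Loss to follow-up adds little: section 2.12 expects fewer than 5 children lost and budgets home visits.
- Even with perfect measurement, the assumed effect has 43% power, so no efficacy conclusion turns on this.

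All of this limits the size of the point. It does not supply the missing end date, which is a matter of data collection and cannot be recovered at analysis.

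**Conclusion.** The point holds as a gap in data collection with a cheap remedy; it is not a contradiction or an error in the plan. As written, recurrence and re-presentation are assessed once, at day 60, and the end of the index episode is not captured for children discharged with symptoms. Misclassification is therefore possible, and it could differ between arms if treatment shortens the index illness.

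Its size is unknown. The rates in the table are assumptions. A reader might also be drawn to a specific number of percentage points of false recurrence difference, obtained by assuming a gap between arms in unresolved diarrhoea. That only returns the gap put in. The 24.5 hours in section 1.1 is a mean reduction in duration and does not say how many children leave hospital unresolved.

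Priority is low to moderate: these are secondary outcomes in a 100-child pilot judged on feasibility. It is worth doing because the pilot sets out to test its outcome methods and event rates.

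**What to change.** Amend sections 2.7 and 2.9.2 as follows.

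- **At the existing 7-14 day contact**, record whether and when the index diarrhoea stopped, and any new episode, visit for diarrhoea or readmission since discharge.
- **At day 60**, ask about the interval since that contact, or since discharge if the early contact was missed.
- **Definition**: count as recurrence only diarrhoea meeting the entry definition in section 2.2.1 after recorded resolution of the index episode.

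The cost is a slightly longer contact and one more form page; treatment and the visit schedule do not change. Recall over the remaining 36 to 51 days (for the assumed stay of 2 to 10 days) is not removed. A further call, diary or record check would be needed for that, at additional cost.

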**2.8 What are the proposed *clinical* outcome measures?**

**2.8.1 Primary clinical outcome.** The primary outcome is mortality. If the participant dies prior to the 60-day followup, the research assistant will determine the date of death as accurately as possible.

**2.8.2 Other clinical outcomes.** Secondary outcomes will include the following: weight z-score at 60-day followup adjusted for initial weight; height z-score at 60-day followup adjusted for initial height; presence of stunting at 60-day followup; length of stay in hospital; number of days with at least three watery stools; number of days of fever in hospital; 7-day mortality; recurrence of acute diarrhoea during the 60-day followup period; re-presentation to a medical professional because of acute diarrhoea during the 60-day followup period; readmission to a paediatric medical ward during the 60-day followup period; HIV viral load (detectable/undetectable) at the next assessment within 6 months of enrollment, for those participants that are HIV positive; and environmental enteropathy score([21](#_ENREF_21)) (composite of faecal alpha-1 antitrypsin, neopterin, and myeloperoxidase) at 60 days.

**2.9 How will the *clinical* outcome measures be measured at follow up?**

**2.9.1 Mortality.** Mortality will be ascertained by the research assistant, whether in hospital or after discharge.

**2.9.2 Secondary clinical outcomes**. Data related to secondary clinical outcomes associated with the participant’s stay in hospital (number of days of 3+ watery stools, number of days of fever, length of stay) will be abstracted from the patient chart (both physician and nursing notes) at discharge. The remaining secondary clinical outcomes will be assessed at the 60-day followup visit; the research assistant will use a calibrated scale and stadiometer to obtain precise anthropomorphic measures.

**2.10 What are the *feasibility* outcomes, or criteria for success of this pilot study?**

The specific feasibility criteria of this pilot are:

1) to enroll at least 100 participants during the 12-month study period;

2) to ensure that >95% of participants have a rectal swab taken within 18 hours of admission;

3) to verify that >95% of rectal swabs in the experimental group are resulted within 48 hours of admission;

4) to ensure >95% of participants found to have a treatable enteric pathogen are prescribed appropriate antimicrobials;

5) to ensure that >95% of participants prescribed antimicrobials start them within 24 hours of the test being resulted;

6) to contact >95% of participants 7-14 days after discharge from hospital; and

7) to contact >90% of participants 60 days after admission to hospital.

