**2.3 What are the planned trial interventions?**

**2.3.1 All participants.** Data to generate Vesikari scores([20](#_ENREF_20)), a validated measure of gastroenteritis severity, will be collected at enrollment, and all study participants will be weighed and measured using calibrated apparatus. Percent dehydration will be abstracted from the paediatric team admission note (subjective dehydration) and will also be calculated comparing weight nadir in hospital to weight at discharge from hospital (objective dehydration). All participants will have a rectal flocked swab taken at enrollment within 18 hours of admission. Most of these children will not be started on antimicrobials at admission, as per current Princess Marina Hospital and World Health Organization standards, excepting children with severe acute malnutrition. Rehydration procedures will be decided by the attending physician; as per Princess Marina Hospital dehydration protocols, all those with severe dehydration receive intravenous rehydration with isotonic fluids and those with mild-moderate dehydration receive WHO-standard oral rehydration solution (ORS). It is standard of care at Princess Marina Hospital to also provide zinc treatment for gastroenteritis.

**2.3.2 Rapid testing and targeted antimicrobial therapy plus probiotic therapy arm.** These participants will be started on *Lactobacillus reuteri* within 24 hours of enrollment**.** All of these participants’ rectal swabs will be processed using our novel diagnostic techniques and resulted within 48 hours. It will be recommended to the attending physician that *Shigella,* ETEC, and *Campylobacter* infections be treated with azithromycin, and *Cryptosporidium* infections be treated with nitazoxanide. It will also be recommended that antimicrobials will be started as soon as possible, preferably on the day the test results become available, and antimicrobials will be provided free of charge. Probiotic therapy will be continued until the measurement of the primary outcome, 2 months post-enrollment.

**2.3.3 Rapid testing and targeted antimicrobial therapy plus placebo therapy arm.** These participants will be started on placebo therapy within 24 hours of enrollment and will have rectal swabs processed rapidly (see 2.3.2). Placebo therapy will be continued until the measurement of the primary outcome, 2 months post-enrollment.

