**2.5 What are the proposed practical arrangements for allocating participants to trial groups?**

A statistician independent of the study will generate a randomization list such that participants can be assigned at random to one of the four study groups in a 1:1:1:1 ratio. The randomization code will be generated by a random number generator and will be blocked (randomly in groups of 4-8), with the random blocking not disclosed. Given the substantial increase in mortality among children with severe acute malnutrition, randomization will be stratified by its presence or absence. Randomization will be communicated to the research assistant using an internet-based system.

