**2.11 What is the proposed sample size?**

For this pilot study, a sample of 100 participants will be adequate to evaluate the feasibility criteria.

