**2.13 What is the proposed type of analysis?**

The principal analysis will be intention-to-treat, i.e. all participants will be analyzed in the groups to which they were randomized, regardless if they received the appropriate antimicrobials (for those in the rapid swab analysis groups) or if they were adherent to the probiotic treatment (for those in the relevant groups). As the primary outcome (mortality) is binary, the chi-square test will be used. The chi-square test will also be used to interpret the following secondary outcomes: presence of stunting at 60-day followup, 7-day mortality, recurrence of acute diarrhoea during the 60-day followup period, re-presentation to a medical professional or readmission to Princess Marina Hospital because of acute diarrhoea in the 60-day followup period, and detectable HIV viral load within 6 months of enrollment. Analysis of covariance or logistic regression will be used to analyze the following secondary outcomes: height z-score at 60 days adjusted for initial height, weight z-score at 60 days adjusted for initial weight, and environmental enteropathy score at 60 days. Survival analysis will be used to analyze the following secondary outcomes: length of stay in hospital, number of days with at least three watery stools, and number of days of fever in hospital. Secondary analyses will attempt to control for the time to initiation of appropriate antimicrobial therapy and the time to initiation of probiotic therapy. Statistical analysis will be conducted using STATA 11.0 (College Station, TX).

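### Feasibility criterion 3 counts swabs, not children randomised to rapid testing, so a rapid-arm child who is never swabbed drops out instead of counting as a failure (minor)

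*Protocol*

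**What the plan says.** Section 2.10 of the protocol lists seven criteria for the success of the pilot, and section 1.2 gives the same list. Two concern the swab and its result:

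- Criterion 2: "to ensure that >95% of participants have a rectal swab taken within 18 hours of admission". The denominator is all participants, rapid and delayed testing together.
- Criterion 3: "to verify that >95% of rectal swabs in the experimental group are resulted within 48 hours of admission". The denominator is swabs. The term experimental group is not defined for this 2x2 design. I read it as the two rapid-testing arms, the only ones with prompt results.

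Section 2.3.1 plans a swab for everybody: "All participants will have a rectal flocked swab taken at enrollment within 18 hours of admission". Section 2.3.2 also states the 48-hour target for swabs: "rectal swabs will be processed using our novel diagnostic techniques and resulted within 48 hours". Section 2.11 asserts that "a sample of 100 participants will be adequate to evaluate the feasibility criteria", without a calculation. For the clinical outcomes, section 2.13 says that "all participants will be analyzed in the groups to which they were randomized".

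**The concern.** Rapid testing can help a child only if a result arrives in time. The natural measure of delivery is therefore the share of children randomised to rapid testing who have a result within 48 hours of admission. None of the seven criteria measures it.

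A rapid-arm child without a swab is absent from criterion 3. That child does count as a miss in criterion 2, but there the miss can be offset by swabs from the delayed arms, which under section 2.3 are batched and processed only after enrolment ends. Criteria 4 and 5 start once a pathogen has been found or an antimicrobial prescribed, so they do not recover the child either.

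At stake is how the pilot's own success threshold is read. Two figures above 95% could be taken to mean that rapid testing reached more than 95% of the children allocated to it, when the per-child figure is lower.

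**Working it through.** There is no stated calculation behind the 100 participants to reproduce. The check is a count.

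**Inputs**
- Total: 100 (section 2.11).
- Allocation: "assigned at random to one of the four study groups in a 1:1:1:1 ratio" (section 2.5). Two of the four groups have rapid testing, so 50 of 100 if allocation is exactly balanced.
- Children with severe acute malnutrition are "eligible to be included in the rapid vs delayed testing and targeted treatment arms" (section 2.2.1). I assume they are split 1:1 between rapid and delayed testing, which leaves the 50 unchanged.
- Threshold: more than 95% for each criterion (section 2.10).

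**Step 1, criterion 2.** 95/100 is not above 95% and 96/100 is, so up to 4 children may miss. I take these 4 as never swabbed; this is an assumption, because the criterion also fails a child whose swab is merely late.

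**Step 2, criterion 3.** Let m of the 4 be in the rapid arms. Then 50 − m swabs remain, and I take the smallest count above 95% of them. In every row this allows two late results and no more (for example 43/46 = 93.5% fails).

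**Step 3, per child.** Divide that count by 50.

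**Step 4, chance of each split.** If 4 misses fall at random over 100 children, P(m) = C(50, m) × C(50, 4 − m) / C(100, 4).

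| Never swabbed in rapid arms (m) | Swabs left | Lowest pass on criterion 3 | Per child randomised | P(m), given 4 random misses |
|---|---|---|---|---|
| 0 | 50 | 48/50 = 96.0% | 48/50 = 96% | 5.9% |
| 1 | 49 | 47/49 = 95.9% | 47/50 = 94% | 25.0% |
| 2 | 48 | 46/48 = 95.8% | 46/50 = 92% | 38.3% |
| 3 | 47 | 45/47 = 95.7% | 45/50 = 90% | 25.0% |
| 4 | 46 | 44/46 = 95.7% | 44/50 = 88% | 5.9% |

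The fourth column is the lowest value compatible with passing both criteria, not the expected value. P(m) gives only the split of the misses; it is not the chance that 4 children go unswabbed, nor that the late-result allowance is used up.

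**Late swabs.** A swab taken after 18 hours fails criterion 2 but stays in the denominator of criterion 3. If all 50 rapid-arm children are swabbed at some time, the first row applies and criterion 3 alone guarantees 48/50 = 96%.

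**With a per-child denominator.** More than 95% of 50 needs 48/50, so 94%, 92%, 90% and 88% all fail. If the true per-child rate were 88%, 90% or 92%, the binomial chance of reaching at least 48/50 would be 5%, 11% or 23%.

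**Possible effect on a main trial.** Suppose a late or absent result gives no benefit, so that the intention-to-treat effect shrinks in proportion to delivery d and sample size grows as 1/d². Measured against the 96% that the per-child criterion itself accepts, the excess is (0.96/0.92)² = 1.09 at 92% and (0.96/0.88)² = 1.19 at 88%.

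**The case against.** The strongest reply is that children who are never swabbed should be rare. A swab is planned for every participant at enrolment, it does not depend on waiting for a stool, and section 2.16.1 reports more than 500 taken without a complication. With one swab planned per child, swabs and children nearly coincide. This stands, and it is why the point is minor. It does not remove the gap, since criterion 2 itself tolerates four misses and does not say that they must be late rather than absent.

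A second reply is that the criteria follow the steps in order (swab, result, prescription, start), so that a failure can be traced to one step, and that criterion 3 targets laboratory turnaround, a concern in sections 1.3 and 2.15. That is a fair use for a per-swab figure, but it can be reported beside a per-child criterion.

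A third is that the per-child rate can be recovered later from the recorded times. It can, but the success threshold would still be judged on another quantity.

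Two stronger readings are tempting and not supported. A reader might infer that delivery of 88-92% is to be expected; these are the lowest passing results, and 88% needs all four misses to be unswabbed rapid-arm children plus two late results. A reader might also infer that a main trial would need 1.18 to 1.29 times the sample (1/0.92² and 1/0.88²). That compares with 100% delivery, gives late results no value, and presumes that criterion 3 will set the main trial's delivery assumption, which the protocol nowhere says.

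**Conclusion.** The point holds in a limited form, and its severity is minor. As worded, criteria 2 and 3 can both pass with 94%, 92% or, in an unlikely worst case, 88% of rapid-arm children having a result within 48 hours of admission, if 1, 2 or 4 of them are never swabbed and two further results are late. If nobody in the rapid arms goes unswabbed, the criterion as written already secures 96%.

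This rests on exactly 100 enrolled, 50 in rapid testing, and the reading of the experimental group given above. Any sample-size consequence is at most about 1.09 (at 92%) to 1.19 (at 88%) over the 96% benchmark, and only if late results give no benefit.

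A reader might infer a breach of the intention-to-treat rule in section 2.13. There is none: that rule governs the clinical analysis, which is unaffected. The defect lies only in how a success criterion is defined. Since the protocol has already fixed the denominators, it is not a detail left open for a statistical analysis plan.

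**What to change.** In sections 1.2 and 2.10, reword criterion 3 along these lines: *>95% of participants randomised to the two rapid-testing arms have a swab result reported within 48 hours of admission; no swab or no result counts as not met.* This also settles which arms are meant. Keep the per-swab turnaround as a descriptive laboratory measure, so that a shortfall can still be traced to collection or to processing. Report criterion 2 separately for the rapid and delayed arms.

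The cost is wording only. The audit in section 3.2 already checks the timing of specimen collection and of results, so no new data are needed. The downside is that the criterion becomes slightly harder to meet: with 50 children it needs 48 timely results, and each unswabbed child uses up one of the two permitted failures.

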**1.3 Why is a pilot study necessary?**

This proposed pilot study is an essential first step prior to conducting an expensive multicentre trial. The process of the study must be verified; we will need to optimize communication between the study nurse and the microbiology laboratory to ensure that study specimens are obtained in a timely fashion, processed completely, and that results are communicated in an efficient manner back to the treating physicians. We will also need to ensure that a mechanism is put in place to ensure follow-up and that all outcomes can be reliably measured. We will likely need to compare various point-of-care assays to determine which will perform optimally in a clinical trial setting.

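### The 60-day success criterion counts contact, and none of the seven criteria requires the 60-day weight, height or stool that the pilot is meant to show can be obtained

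*Protocol*

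**What the plan says.** Protocol section 2.10 lists seven feasibility criteria, which also appear in section 1.2. Two concern follow-up. Criterion 6 is "to contact >95% of participants 7-14 days after discharge from hospital" and criterion 7 is "to contact >90% of participants 60 days after admission to hospital". Neither defines contact or says how a child who has died is counted.

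Other sections describe what the two contacts are for:

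- **7-14 days after discharge (section 2.7):** a reminder, "to ensure that the caregivers remember the timing of the second follow-up visit", and a chance to ask questions. No measurement is scheduled.
- **60 days (section 2.7):** "to assess the primary outcome and weigh and measure the participant, if applicable".
- **60-day measurements (section 2.9.2):** "The remaining secondary clinical outcomes will be assessed at the 60-day followup visit", and "the research assistant will use a calibrated scale and stadiometer to obtain precise anthropomorphic measures".
- **60-day stool (section 2.4):** a sample is taken at the two-month visit for the environmental enteropathy score.

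Section 1.3 gives as one reason for the pilot the need to "ensure that a mechanism is put in place to ensure follow-up and that all outcomes can be reliably measured". Section 2.11 says that "a sample of 100 participants will be adequate to evaluate the feasibility criteria", without a derivation.

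**The concern.** The pilot exists to show that the main trial can be run, and section 1.2 asks that trial to answer a question about mortality and stunting at 60 days. Stunting and the two growth z-scores need a child on a scale and a stadiometer; the enteropathy score needs a stool sample. A telephone call provides none of these, and section 2.2.2 makes telephone access a condition of eligibility, so calls will nearly always be possible.

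The criterion can therefore be met while the growth and enteropathy outcomes are largely missing. The team would then plan a large multicentre trial on a pilot that met its follow-up target without testing whether families return, or can be visited, for measurement.

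A smaller matter is the denominator of criterion 6. It is all participants, but a child who dies in hospital is never discharged and so has no post-discharge window.

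**Working it through.** **Coverage of the criteria.** The seven criteria cover, in order: enrolment, swab timing, result timing, prescribing, start of antimicrobials, early contact and 60-day contact. None mentions 60-day weight, height or stool.

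**Inputs**

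- n = 100 (section 2.11). No precision or power is given for this number, so there is no calculation to reproduce.
- Loss to follow-up 1/60 = 1.67%, from the team's other studies at 3 months (section 2.12). This gives 100 × 1/60 = 1.7 expected losses, consistent with the protocol's expectation of fewer than 5.
- Mortality 3.2%, from a cited cohort of children with moderate-to-severe diarrhoea in sub-Saharan Africa (section 1.1). It is not a forecast for this trial. The values 1% and 2% for deaths before the early contact are assumptions.

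**Criteria as counts.** More than 95% of 100 means at least 96 contacted, so at most 4 misses. More than 90% means at least 91, so at most 9 misses.

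**Gap between contact and measurement.** The expected number of children alive and reached is 100 × (1 − 0.032) × (59/60) = 95.2. The share of these seen in person is an assumption:

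| Share seen in person | Children measured per 100 enrolled | Contact count for criterion 7 |
|---|---|---|
| 100% | 95 | 95, met |
| 80% | 76 | 95, met |
| 50% | 48 | 95, met |

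The contact count is the same in every row, so criterion 7 cannot tell these situations apart. Likewise, 95 families reached and 70 children measured would meet it, with 30 of 100 growth measurements absent.

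**Effect of deaths if they were counted as misses.** Contact probability is c = (1 − mortality) × (1 − 1/60), taking death and loss as independent. The chance of meeting a criterion is the exact binomial probability of at least 96 (criterion 6) or 91 (criterion 7) contacts in 100.

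| Mortality before the contact | Expected misses | Criterion 6 met | Criterion 7 met |
|---|---|---|---|
| 0 (losses only) | 1.67 | 0.974 | >0.999 |
| 1% | 2.65 | 0.873 | >0.999 |
| 2% | 3.63 | 0.701 | 0.996 |
| 3.2% | 4.81 | 0.470 | 0.978 |

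For criterion 6 the 3.2% row is a worst case: it puts every death before a contact made 7-14 days after discharge, and it applies a 3-month loss rate to that early contact. For criterion 7 the same row changes little.

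**The case against.** The best defence is that the planned 60-day contact is plainly in person. Section 2.7 includes weighing and measuring, section 2.9.2 describes a visit with equipment, section 2.4 takes stool at that visit, and section 2.12 budgets home visits for families who do not return. Section 1.2 adds that follow-up and outcome assessment methods will all be assessed, so completeness would be looked at anyway. The primary outcome is mortality, for which reaching the family is enough, and definitions can be left to an analysis plan. The 70-of-100 scenario is invented.

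This is right about intent: nothing suggests that the team means to telephone instead of visit. But the criteria for success are fixed in the protocol, and they do not check that the intended visit took place. A general statement that methods will be assessed sets no target.

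Three stronger readings are tempting and are not supported:

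- **Deaths use up the allowed misses.** The protocol does not say so. Contact with a child under five means contact with a caregiver, who can be reached after a death. Section 2.7 makes assessing mortality a purpose of the 60-day contact, section 2.8.1 has the research assistant establish the date of death, and section 2.9.1 covers deaths in hospital and after discharge. Serious harm to criterion 7 would need a mortality well above 3.2%, and the documents give no such figure.
- **A telephone call also makes criterion 6 too weak.** It does not. A reminder and answers to questions are all that is planned at that point.
- **Missing one criterion stops the main trial.** No such rule is stated. The stated goal is to demonstrate feasibility.

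**Conclusion.** The point holds for criterion 7. It measures contact, not completeness of outcomes, and no other criterion fills the gap, although section 1.3 makes reliable measurement of all outcomes part of the reason for the pilot. This follows from the wording and rests on no numerical assumption. How large the gap would be in practice is unknown; the shares seen in person used above are illustrative.

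On deaths, only a minor wording point remains, for criterion 6. A child who dies before discharge has no contact window, and the criterion does not say how that child is counted. If early deaths were treated as misses, the chance of meeting criterion 6 would drop from 0.974 to between 0.87 and 0.70 at an assumed 1-2% early mortality, and to 0.47 in the worst case. These figures assume 1/60 loss and independence of death and loss. A reader might infer that deaths could also cause criterion 7 to be missed. At the cited 3.2% the probability of meeting it is still 0.978, and section 2.7 supports counting an established death as a completed contact.

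**What to change.** In sections 1.2 and 2.10:

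1. Restate criterion 7 as 60-day vital status known for more than 90% of participants, with an established death counted as known.
2. Add a criterion that weight, height and the stool sample are obtained at the 60-day visit in a stated proportion of survivors, for example more than 90%. The protocol gives no basis for a particular figure, so the team should choose one from the missingness that the main trial could tolerate.
3. Minor: base criterion 6 on participants discharged alive, and count a death learned at that contact as successful contact.

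The cost is wording. The measurements, the stool sample and the home visits are already planned, so no procedure is added. The downside is that the new criterion is harder to meet than contact alone, and the pilot may miss it where it would have met criterion 7 as now worded.
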